#### Relevant concomitant care permitted or prohibited during the trial {11d}

Treatments concomitant to the study will be allowed if not related to changes in research outcomes (e.g., simple dressing or hydration of the intact skin near the edge of the wound).

#### Provisions for post-trial care {30}

Provisions for post-trial care are not applicable in this study due to the nature of the intervention. All harms and adverse events will be properly managed. Participants will be referred to the respective referral services in case of health problems due to study procedures, and specialized medical assistance will be offered at no cost.

### Outcomes {12}

Participants will initially undergo an anamnesis to identify the presence of diabetes or other diseases interfering with biophysical aspects of the skin or characteristics of the burn. Evaluations will be conducted by a trained external evaluator blinded to allocation.

#### Primary outcome measures

##### Re-epithelialization rate

The percentage of healed skin tissue (re-epithelialization rate) and the number of days between the start of treatment and total healing process will be assessed using digital images of the burned region. These images will be captured daily from before treatment to follow-up of the re-epithelialization process. A digital camera (Sony Cyber-Shot Dsc-W800, 20.1 megapixels, Brazil) will be positioned on a tripod, parallel to the ground and perpendicularly fixed at a distance of 30 cm from the area to be treated. If the participant cannot stand, images will be captured on a stretcher assuring the same distance and a 90° angle between the area and the camera. The photograph will be captured on a white background with indirect artificial lighting.

Re-epithelialization rate will be assessed by counting the days until complete healing and monitoring the wound area during protocols (ImageJ® software, version 1.36 b). The crust area on the wound edge will be measured using digital image analysis, according to Gabison et al. [19]. The software converts the selected area to cm^2^ by associating the known dimension of the photographed object, area of interest, and the respective number of pixels. Healing will be assessed using a glossary of healing evolution based on the pressure ulcer assessment scale proposed by Bates-Jensen, Vredevoe, and Brecht [20].

#### Secondary outcome measures

##### Skin temperature

Thermographic evaluation will be conducted at the League of Studies in Dermatofunctional Physiotherapy of the Federal University of Paraíba, with room temperature between 22 and 24 °C and relative humidity of 43.0 ± 0.1% (monitored by thermohydrometer).

Participants will be previously instructed to avoid eating foods that alter thermogenesis, using body creams or oils, and wearing clothes that expose the region to be evaluated. Participants will also undergo a 15-min acclimatization to adapt to room temperature. Images will be taken with participants in orthostatic position. Thermograms will be obtained using a FlirOne camera (FLIR Systems, Inc., Wilsonville, OR) with an IR resolution of 120 × 160 pixels, temperature range from − 20 to 120 °C, and thermal sensitivity of 0.1°C. The camera will be fixed on a tripod parallel to the ground, with height adjusted to create a 90° angle with the region of interest, and at a distance of 30 cm. The distance from the camera to the area will be measured using a ruler fixed by the metallic support. If the volunteer cannot stand, images will be captured on a stretcher using the same metallic support to assure distance and angle between the area and the camera. FLIR tools software will process and analyze thermographic images.

##### Pain and local pruritus 

Pain intensity in the treated area will be assessed daily, before therapy, and until the end of treatment using the visual analog scale (VAS). This scale consists of a graduated line with scores ranging from 0 to 10 (0 represents “no pain” and 10 “worst pain possible”). Pain using VAS can be classified as mild (up to 3 points), moderate (from 4 to 7 points), or severe (> 7 points). Individuals will be asked to indicate the number on the scale that represents pain intensity.

The intensity of pruritus will also be assessed daily, before therapy, and until the end of treatment using the Itch Severity Scale, translated and validated to Brazilian Portuguese [21] and adapted for individuals with burn wounds. The scale consists of seven questions (description, frequency, intensity, extension of pruritus, and how pruritus affects sleep, mood, and sexual activity or desire), ranging from zero to one. The total score is obtained by the sum of all questions multiplied by a correction factor (×3) and ranges from 0 (no pruritus) to 21 points (most severe pruritus); minimal important difference is 2 points.

##### Scar mobility in the burned area 

After complete healing, an adheremeter will be positioned (without direct contact) in the central point of the scar most adhered to the skin. The skin will be stretched by centrifugation in four orthogonal directions (caudal, rostral, right, and left sides). Maximum distension will be read on the instrument after each traction. After releasing the tension, the researcher will observe if the landmark will return to the starting point; if not, the measurement will be repeated. This procedure will also be performed at the same location on the contralateral limb [22].

##### Quality of wound healing

The Vancouver scale will assess the quality of wound healing. It analyzes aspects of healing (e.g., vascularization, pigmentation, flexibility, and scar height) and presents a total score ranging from 0 (normal) to 13 (poor).

#### Participant timeline {13}

Figure 2 represents an overview of the study design and main procedures.

**Fig. 2 Fig2:**
[figure not shown]
Participant timeline

Sociodemographic data, characteristics of the burn (i.e., type of accident, causal agent, and percentage of body surface affected), when the burn happened, and pharmacological treatment received will be registered on an evaluation form. Participants will be instructed to maintain standard care. A trained researcher will assess and perform therapeutic procedures five times a week, once daily. Wound healing rate, pain, pruritus, skin temperature, mobility restriction, and scar quality will be analyzed.

Digital images of the burned area, skin temperature (infrared image), and pain and pruritus will be assessed daily before therapeutic procedures. Only three assessments will be analyzed: initial (before treatment), final (when re-epithelialization of the burn is complete), and one assessment between initial and final assessments (median time of treatment between initial and final assessment). After treatment and total wound closure, mobility and scar quality will be assessed using the adheremeter and Vancouver Scale, respectively.

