### Study objectives

#### Primary objective

The primary objective is to determine whether LED photobiomodulation is superior to simulation to increase the re-epithelialization rate and decrease the healing time of burn wounds.

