## Statistical methods

### Statistical methods for primary and secondary outcomes {20a}

Outcome variables will be re-epithelialization rate, presence and intensity of pain and pruritus, local skin temperature, and scar mobility and quality. Groups will be considered independent variables. Statistical analysis will be performed according to intention-to-treat principles. Descriptive analyses and histogram inspections will determine data normality. Between-group differences and 95% confidence intervals (95% CI) will be calculated using linear mixed models and group, time, and group-versus-time interaction terms. A first-order autoregressive covariance matrix will be considered. Group and time will be considered fixed factors, and participants the random factors. A Q-Q plot will be performed for all variables to consistently and similarly confirm the normality of residues between groups. The SPSS software version 20.0 (IBM SPSS Corp., Armonk, NY) will be used for data analysis.

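### The three analysed assessments are tied to each participant's own closure date, so the group-by-time analysis of percent healed reads the shape of the healing curve and not its speed

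*Protocol article*

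**What the plan says.** All references are to the protocol article.

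- **Outcomes {12}, Re-epithelialization rate.** The primary outcome has two components: "The percentage of healed skin tissue (re-epithelialization rate) and the number of days between the start of treatment and total healing process". A later sentence merges them: "Re-epithelialization rate will be assessed by counting the days until complete healing and monitoring the wound area during protocols". On images: "These images will be captured daily from before treatment to follow-up of the re-epithelialization process".
- **Primary objective.** The aim is to show whether "LED photobiomodulation is superior to simulation to increase the re-epithelialization rate and decrease the healing time of burn wounds".
- **Participant timeline {13}.** Of the daily data, "Only three assessments will be analyzed: initial (before treatment), final (when re-epithelialization of the burn is complete"). The third analysed point lies in the middle of the course, and its timing is given as the "median time of treatment between initial and final assessment".
- **Statistical methods {20a}.** One model is given: a linear mixed model with group, time and their interaction. "A first-order autoregressive covariance matrix will be considered". The outcome list names the re-epithelialization rate but does not list days to healing separately.
- **Sample size {14}.** The trial is sized on the re-epithelialization rate by repeated-measures ANOVA: effect size 0.5, 80% power, alpha 0.05, 30 participants in three groups of ten, raised to 39.

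**The concern.** The rule uses the outcome to choose when the outcome is measured. The last analysed assessment exists because the wound has closed, so percent healed there is fixed. The first is fixed as well, because healing is measured from the baseline wound. The middle one slides with the closure date: a wound closing in 8 days is read at day 4, one closing in 16 days at day 8. A treatment that halves healing time can leave all three analysed values unchanged.

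This is the repeated-measures analysis on which the trial is sized. It could report no effect on the rate when healing is faster, or a significant effect when curves differ in shape but wounds close at the same time. Participants who drop out or do not close have no final assessment, and so no midpoint, although the analysis is declared intention-to-treat.

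**Working it through.** **Inputs.** From the article: the three-assessment rule, percent healed as outcome, the model, the sample-size inputs, and a healing range of 7 to 21 days (Background {6a}). Assumed, because not given: correlation 0.5 between assessments, mean closure times, coefficient of variation (CV) and curve shapes.

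**1. The plan's own figure.** For the between-group effect in repeated-measures ANOVA, lambda = f²·N·m / (1 + (m − 1)·rho). With f = 0.5, N = 30, m = 3 and rho = 0.5, lambda = 0.25 × 30 × 3 / 2 = 11.25 on (2, 27) degrees of freedom, giving power 0.817. Thirty is the smallest multiple of three reaching 80%. The figure therefore fits a three-assessment analysis, although other settings also give 30 (for example m = 2, rho = 0.3).

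**2. What the three values can carry.** Let T be a participant's closure time and h(t/T) the percent healed at time t. The analysed values are h(0) = 0, h(0.5) and h(1) = 100. T does not appear. If curves share a shape, neither the interaction nor the group main effect can register a difference in T.

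| Closure (days) | Linear, own midpoint | Linear, day 5 | Exponential to 1% residual, own midpoint | Exponential, day 5 |
|---|---|---|---|---|
| 7 | 50% | 71% | 90% | 96% |
| 10 | 50% | 50% | 90% | 90% |
| 14 | 50% | 36% | 90% | 81% |
| 21 | 50% | 24% | 90% | 67% |

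**3. Rejection rates.** Three-group test at 5%, percent healed = 100·(t/T)^k with k varying between participants, CV of closure time 25%, 2,000 runs. The common day is half the pooled median closure time.

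| Mean closure (red, infrared, sham) | n per arm | Own midpoint | Common day | Days to closure |
|---|---|---|---|---|
| 10, 10, 14 | 10 | 5.1% | 51% | 84% |
| 10, 10, 14 | 13 | 5.3% | 66% | 93% |
| 7, 7, 21 | 10 | 4.8% | >99% | 100% |
| 14, 14, 14, with k centred on 0.7, 0.7, 1 | 10 | 74% | 30% | 5% |

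The last row is the reverse error: closure times are equal, but curves differ in shape (at central k, 100 × 0.5^0.7 = 62% against 50% at the midpoint).

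A pairwise version (ten per arm, sham mean 14 days, LED 9.8 days, CV 0.3) gives a midpoint difference of 0.0 points with 5% rejection. At a common day 7 the difference is about 20 to 21 points, with 57 to 68% power depending on how much shapes vary. A test on log days to closure has roughly 70% power.

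**4. Covariance, for percent healed.** The variances at the three points are 0, σ² and 0. A single common variance averages them to σ²/3, so the midpoint standard error is too small by √3. A nominal 5% pairwise test then rejects with probability 2·(1 − Φ(1.96/√3)) = 2·(1 − Φ(1.13)) = 0.26 under no effect, assuming normal data. Simulation agrees (about 26%), and the interaction test rejects about 10%.

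**5. Pain, itch and temperature.** These are not fixed at either end, so steps 2 and 4 do not apply. The timing problem does: the arms are compared at different elapsed days if closure times differ.

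**The case against.** **Days to healing is in the primary outcome.** This stands. The outcome section counts days to complete healing, the primary objective names healing time, and the final assessment is itself the closure date. A reader might infer that the trial cannot show faster healing. The article does not support that: the day count is untouched by the three-assessment rule and is the more powerful measure in every closure-time scenario above. What remains is that a single value per participant cannot enter a group-by-time model and that no other analysis is stated. An analysis plan not shown may supply one, but it would not remove the explicit restriction to three assessments.

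**The null midpoint result is built in.** Also fair. T cancels because LED is assumed only to rescale time. If LED instead raised the healing rate 1.8-fold for the first 5 days only (linear healing, sham mean 14 days, measurement SD 8, ten per arm), the own-midpoint difference was 9 points with 63% rejection, against 61% for days to closure. So it would go too far to say that an effective LED must be reported as ineffective. The result depends on the form of the effect, which the article does not specify.

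**The AR(1) error is not general.** Correct. For wound area in cm², which is also monitored, baseline areas vary, the pooled variance exceeds the midpoint variance, and the nominal 5% test rejects only about 1 to 3%. The claim that standard errors are too small holds for percent healed alone. The equal-variance form is the ordinary reading of AR(1), but the article does not spell it out.

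**Symptoms at matched healing stages are a legitimate comparison.** They are, and these outcomes are not uninformative. They answer a different question from whether symptoms fall sooner.

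**The middle time might be one common day.** Possible, and the middle value would then carry speed information. The wording ties it to the interval between a participant's first and last assessments, and the number of sessions is not fixed, so the own-midpoint reading is more natural. Two of the three values stay fixed on either reading.

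**Conclusion.** The point holds for percent healed in the stated group-by-time model, and it should be corrected before unblinding. Two of three analysed values are constants. On the natural reading of the middle time point, the third reflects curve shape: rejection is about 5% for a pure speed-up of any size examined, and 74% for a shape difference with no difference in closure. The 0% and 100% values follow from the definitions alone. The midpoint result rests on LED compressing the curve without changing its shape. The power figures for common days and for closure time rest on assumed closure times, CV and shapes, since the article gives only a 7 to 21 day range.

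The conclusion does not extend to the whole trial, because days to closure remains informative, nor to pain, itch and temperature beyond the change of question. The 26% error rate is limited to percent healed with equal-variance AR(1) and normal data.

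**What to change.** Replace the three-assessment rule.

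1. Analyse percent healed at prespecified common days from the start of treatment, using the daily images. Take the nearest session, since sessions run five times a week, and count a closed wound as 100% from closure onward.
2. Use an unstructured or heterogeneous-variance covariance in place of AR(1).
3. State days to closure as a primary-outcome analysis in its own right: time-to-event from the start of treatment, with censoring for wounds not seen to close. Say how it and percent healed together answer the primary objective.
4. Use the same common days for pain, itch and temperature. Pain and itch are scored only until treatment ends, so choose days on which most wounds are still open, or state how participants already closed are handled.

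The cost is a protocol and registry amendment before unblinding and more image tracing. No new visits are needed. Percent healed at a common day still responds to curve shape, but there a difference means more skin healed by that day.

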### Eligibility criteria {10}

We will include participants of both sexes who suffered second-degree burns, aged over 18 years, with good mental health (assessed using the Mini-Mental Status Exam) [18], without pre-existing metabolic diseases or infection in injured tissues, not under pharmacological treatment that alters the healing process (e.g., corticosteroids, chemotherapy, or radiotherapy), and who agree to participate in the research by signing the informed consent form.

Participants will be excluded if they develop dermatological diseases or infectious processes or wish to withdraw from the study for bioethical reasons.

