#### Intervention description {11a}

All protocols will be performed using the Endophoton Esthetic Multi equipment (KLD - Brazil), calibrated according to the manual of the manufacturer (Amparo, São Paulo, Brazil). During application in all groups, the researcher and individuals will wear glasses with an eye protection filter for light radiation (suitable for applicators with wavelength between 415 and 904 nm) with minimum attenuation of 95%. The treatment protocol will be performed with individuals in dorsal decubitus and exposing the area to be treated. Photobiomodulation will last until complete re-epithelialization without a predetermined number of sessions, and duration of each session will occur according to wound size.

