#### Strategies to improve adherence to interventions {11c}

Attrition will be considered in case of missing two consecutive or three alternating sessions, inability to complete assessments after treatment and follow-up, and developing any disabling condition preventing the individual from participating in the study. Regarding adherence strategies, flexible schedules will be offered, and participants will be contacted by telephone to confirm evaluation dates. Additional measures to prevent dropouts will also be applied, including periodic assessments of satisfaction with treatment, discussion of difficulties in continuing treatment (e.g., logistics of visits to the laboratory or home care), and attempts to resolve and avoid potential problems affecting adherence. Furthermore, guidance regarding wound care and treatment will also be offered to increase adherence.

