#### Sample size {14}

Randomized controlled trials conducted with participants with burn wounds are scarce, hindering the calculation of the effect size. Thus, a conservative effect size (0.5), 80% power, and 95% probability (*α* = 0.05) were used for the primary outcome (re-epithelialization rate), generating a sample size of 30 participants (three groups of ten participants). The sample size for repeated measures ANOVA was calculated using the G* Power 3.1.0 software (Christian-Albrechts-Universitat, Kiel, Germany). Considering a possible sample loss of 30%, we intend to recruit 39 participants.

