### Methods in analysis to handle protocol non-adherence and any statistical methods to handle missing data {20c}

We propose an intention-to-treat analysis considering all participants, regardless of the randomized treatment. The intention-to-treat analysis will be applied using a mixed linear model, which treats missing data randomly.

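### The analysed assessments are defined by healing, so a participant lost before healing contributes only a baseline value although daily images exist

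*Protocol article*

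**What the plan says.** - Participant timeline {13} limits the analysed data: "Only three assessments will be analyzed: initial (before treatment), final (when re-epithelialization of the burn is complete". The remaining assessment is placed at the median time between those two.
- Primary outcome measures defines the primary outcome as percent of tissue healed and days to total healing, both read from photographs: "These images will be captured daily from before treatment to follow-up of the re-epithelialization process".
- Intervention description {11a} sets no last day: "Photobiomodulation will last until complete re-epithelialization without a predetermined number of sessions".
- Section {20a}: "Statistical analysis will be performed according to intention-to-treat principles". The model is a linear mixed model with group, time and their interaction.
- Section {20c}: "We propose an intention-to-treat analysis considering all participants, regardless of the randomized treatment". It relies on the mixed model to deal with missing data.
- Participants can leave before healing. Section {11c}: "Attrition will be considered in case of missing two consecutive or three alternating sessions". Eligibility criteria {10}: "Participants will be excluded if they develop dermatological diseases or infectious processes or wish to withdraw from the study for bioethical reasons".
- Sample size {14}: "Considering a possible sample loss of 30%, we intend to recruit 39 participants".

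The protocol gives no substitute final or middle assessment for someone not seen to heal, such as a fixed day or the last image.

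**The concern.** A mixed model copes with dropout by using what was seen of a participant before they left. Here the timeline section removes exactly those values. The final assessment exists only once the wound has closed, and the midpoint can be placed only once the final date is known. A participant who leaves unhealed on day 8 may have a week of photographs, none of which is analysed after the first.

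The post-baseline comparison then rests in effect on participants seen to heal. The missing-at-random assumption behind {20c} also loses the observations that would make it more plausible. With 13 per arm, discarding data already collected is costly.

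Tying the assessment times to healing has a second consequence that does not depend on dropout: it removes most of the contrast between arms in percent healed.

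**Working it through.** **1. The plan's own figure.** Inputs from Sample size {14}: effect size 0.5 (taken as Cohen's f), α = 0.05, power 80%, repeated measures ANOVA, three groups. The number of measurements m and their correlation ρ are not stated; I assume m = 3 and ρ = 0.5. For the between-groups test, λ = f²·N·m / (1 + (m − 1)ρ) with 2 and N − 3 degrees of freedom. At N = 30, λ = 0.25 × 30 × 3 / 2 = 11.25, the critical F is 3.354 and power is 0.817. This reproduces the 30. The recruitment target is 30 × 1.30 = 39.

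**2. What each participant supplies.**

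| | Initial | Midpoint | Final | Days to healing |
|---|---|---|---|---|
| Seen to heal | yes | yes | yes | yes |
| Lost before healing | yes | cannot be placed | does not exist | none |

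**3. What the three times can show.** Percent healed is 0 at the initial assessment and 100 at the final one for every participant in every arm. Only the midpoint is free to vary, and even that depends on the shape of the healing curve. If healing were linear, percent healed on day t would be 100·t/T, with T the healing time; at t = T/2 it is 50 whatever T is. As an illustration with assumed times, a wound closing in 10 days and one closing in 14 both read 0, 50, 100. By calendar day they separate: at day 7 they read 70 and 50. Wound area in cm² is likewise 0 for everyone at the final assessment.

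**4. How many participants are affected.** If 39 yields 30, losses are 9 (9/39 = 23%, 3 per arm). At a literal 30%, 0.30 × 39 = 11.7, about 12. Planned analysed values are 39 × 3 = 117. If every loss precedes healing, each costs two values, leaving 117 − 18 = 99 or 117 − 24 = 93. These are worst cases.

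**5. Power in the plan's own model.** With 9 losses the informative number is 30, the planned size, and power stays at 0.82. With 12 it is 27: λ = 0.25 × 27 × 3 / 2 = 10.125 and power is 0.77 (0.86 at ρ = 0.3, 0.65 at ρ = 0.8). This describes the sample-size model, not the narrower contrast left by step 3.

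**6. Bias in days to healing among those seen to heal.** All healing times and leaving rules here are assumed.
- Constant daily risk of 0.025, mean healing 12 v 16 days, SD 4, losses of 26% and 33%: true difference 3.96 days, healed-only 3.93.
- Leaving correlated 0.3 or 0.5 with healing time, 9/39 lost, true benefit 0.50 SD: healed-only 0.48 and 0.44 SD.
- Leaving only on days 3 to 10: healed-only 0.49 to 0.53 SD against a true 0.51.
- No effect and the same leaving rule in each arm: zero bias.
- Single-arm means shift slightly even without differential loss. With a constant risk of 0.021 per day and whole-day counting, the sham mean is 14.2 days instead of 14.5.

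**7. What daily images recover.** Assumed mean healing 14 v 12.25 days, SD 3.5, leaving on days 3 to 10. The day-7 difference in percent healed is 7.97 points with full data, 7.91 to 8.03 from a daily-image mixed model, and 8.17 to 8.54 among the healed only. At day 14, when leaving is correlated with the wound area seen, the daily model gives 3.09 to 3.45 against 3.80, which is 9% to 19% too low.

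**The case against.** Several objections carry weight.

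- **Intention-to-treat is not broken in form.** A reader might infer that the timeline section contradicts {20a} and {20c}. It does not: a mixed model retains a baseline-only participant in the assigned arm. What is lost is that person's information.
- **The loss in numbers is already budgeted.** A reader might compare 10 v 10 with 13 v 13 and report a standard error 14% wider, √(2/10) / √(2/13) = 0.447 / 0.392. That is a generic comparison of means, not the planned model, and ten per group is the size the plan is powered on. I do not rely on it.
- **Not all losses precede healing.** Attrition in {11c} includes failing to complete assessments after treatment, and {18b} plans to contact participants to complete follow-up. Neither {11c} nor the exclusion rule in {10} says clearly that measurement stops. The counts of 9 and 12 are therefore ceilings.
- **Bias is small.** Step 6 agrees. A reader might infer that a true benefit is necessarily diluted; one scenario gives slight inflation instead.
- **Censoring is often left to an analysis plan.** True, and its absence alone would be no finding. The restriction to three assessments, however, is an explicit instruction, and a later rule using other images would contradict it.
- **The midpoint might mean a group median.** The wording points to each participant's own interval. Even on the other reading, a participant not seen to heal has no final assessment.

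The restriction itself survives: values already collected are discarded for the very participants whose missing data the model is meant to handle.

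**Conclusion.** The point holds as a matter of information. Anyone lost before healing is reduced to a baseline value, and percent healed can differ between arms only at the midpoint, or not at all under linear healing. At most 9 to about 12 of 39 participants are affected through loss; the number lost before healing is not stated. In the plan's own power model this ranges from no change against the planned 0.82 to 0.77, assuming three measurements correlated at 0.5.

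The documents do not support a claim that the trial abandons intention-to-treat or that its result will be materially biased. Bias in the between-arm difference is likely small, can go either way, and is zero under no effect with equal leaving rules. The plan should be changed because the information is already collected and the remedy is cheap.

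**What to change.** - **Participant timeline {13} and {20a}:** analyse wound area and percent healed from all daily images up to closure or the participant's last image, by day since the start of treatment, in the planned mixed model. Enter 0 cm² and 100% healed on days after observed closure.
- **Days to healing:** analyse as time to event, with participants not seen healed censored at their last image.
- **Eligibility criteria {10}:** state that participants who develop infection or skin disease may stop treatment but remain in follow-up and in the analysis.

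The cost is wording plus ImageJ measurement of photographs the plan already takes; no participants or visits are added. There are two statistical drawbacks. Healed values pile up at the boundary, so the residual check already planned in {20a} needs particular attention. Some bias at late days remains if leaving depends on slow healing, as step 7 shows for day 14.

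### On the natural reading, percent healed is analysed at each participant's own halfway point, so it measures the shape of the closure curve and not its speed

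*Protocol article*

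**What the plan says.** The primary objective is to show that LED is superior to simulation "to increase the re-epithelialization rate and decrease the healing time of burn wounds". Under Primary outcome measures, the article gives two components: "The percentage of healed skin tissue (re-epithelialization rate) and the number of days between the start of treatment and total healing process". On the images it says: "These images will be captured daily from before treatment to follow-up of the re-epithelialization process".

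The text after Fig. 2, in Participant timeline {13}, then narrows what is used: "Only three assessments will be analyzed: initial (before treatment), final (when re-epithelialization of the burn is complete". The third, which falls in the middle, is described there as "one assessment between initial and final assessments (median time of treatment between initial and final assessment". Intervention description {11a} leaves the length of treatment open: "Photobiomodulation will last until complete re-epithelialization without a predetermined number of sessions".

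Statistical methods {20a} fits a linear mixed model with group, time and their interaction, with group and time as fixed factors. Sample size {14} is set for the re-epithelialization rate by repeated measures ANOVA (effect size 0.5, 80% power, alpha 0.05) and arrives at 30 participants.

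**The concern.** The final assessment is defined by the event itself, so it falls on a different day for each participant. A midpoint between start and that event is a fraction of the participant's healing time. Healing time is what LED is meant to shorten. Aligning percent healed to a fraction of the outcome removes the difference in speed that the primary objective asks about.

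At stake is the percent-healed half of the primary outcome, for every participant who completes. A real benefit could appear there as no difference, or as a difference in the wrong direction, beside a shorter healing time in the other half. The article would then have to explain two primary results that disagree only because of when the image was chosen.

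**Working it through.** **1. The plan's own figure.** Inputs from Sample size {14}: effect size 0.5 (read as Cohen's f), alpha 0.05, 80% power, three groups. Three assessments come from Participant timeline {13}. The article gives no correlation between repeated measures; 0.5 is assumed. For the between-group effect in a repeated measures ANOVA, lambda = f² × N × m / (1 + (m − 1) × rho) = 0.25 × 30 × 3 / (1 + 2 × 0.5) = 11.25, with 2 and 27 degrees of freedom. Power is 0.817, so 30 is reproduced. The other repeated-measures variants with f = 0.5 and three measures need 9 (within factor) or 12 (interaction). The stated 30 therefore fits a group effect averaged over three measures.

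**2. What the three measures can show.** Let T be a participant's healing time and h the share healed as a function of t/T.

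| Assessment | Time | Percent healed |
|---|---|---|
| Initial | 0 | 0 for all |
| Middle | T/2 | 100 × h(0.5) |
| Final | T | 100 for all completers |

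T does not appear in the last column. If LED shortens T and leaves h unchanged, the expected difference is exactly zero for any curve shape. A difference d at the midpoint gives d/3 as the group effect averaged over the three times, because the other two contribute zero. If wound area in cm² is used instead, the middle value is still a fixed fraction of baseline area and the final value is 0.

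**3. When the shape does change.** Assume a linear curve with sham closing at day 14, and a change of speed at 50% healed.

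| Effect of LED | T (days) | Midpoint (day) | Percent at midpoint | Difference from sham |
|---|---|---|---|---|
| None (sham) | 14 | 7 | 50.0 | – |
| Even, T × 0.7 | 9.8 | 4.9 | 50.0 | 0 |
| Late half doubled | 7 + 3.5 = 10.5 | 5.25 | 5.25 × 100/14 = 37.5 | −12.5 |
| Early half doubled | 3.5 + 7 = 10.5 | 5.25 | 50 + 1.75 × 100/14 = 62.5 | +12.5 |

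The last two rows have the same healing time and opposite signs.

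**4. Simulation.** Ten participants per arm, 4,000 trials per scenario, one-way ANOVA across the three arms at alpha 0.05. Assumed: healing time mean 14 days, SD 3.5, kept within the 7 to 21 days in the Background; varying curve shape (log SD 0.25); reading error SD 5 points. Entries are LED minus sham, with the share of trials significant in brackets.

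| Effect of LED | Own midpoint (points) | Day 7 (points) | Days to healing |
|---|---|---|---|
| None | +0.1 (0.047) | 0.0 (0.049) | 0.0 (0.048) |
| Even, T × 0.7 | 0.0 (0.053) | +20.0 (0.71) | −4.2 (0.90) |
| Late half doubled | −12.2 (0.83) | +5.4 (0.08) | −3.5 (0.74) |
| Early half doubled | +12.6 (0.92) | +24.0 (0.93) | −3.4 (0.72) |

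These test single time points and do not fit the full mixed model. Their sizes depend on the assumptions; the zero for even acceleration does not.

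**5. Ceiling on a later common day.** With a lognormal healing time, mean 14 and SD 4, the log SD is √ln(1 + 16/196) = 0.280 and the log mean is ln 14 − 0.280²/2 = 2.600. The share of sham wounds closed by day 14 is Φ((2.639 − 2.600)/0.280) = Φ(0.14), about 56%. With T × 0.7, closure by day 14 needs an untreated time of at most 20 days: Φ((2.996 − 2.600)/0.280) = Φ(1.41), about 92%.

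**The case against.** Four points can be made for the plan.

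- **Days to healing is also primary and does not use the midpoint image.** This stands. A reader might infer that the trial cannot detect faster healing, or that an effective LED would be reported as null or harmful. The documents do not support that. The objective and the outcome section both name healing time, and in the simulation it picks up all three kinds of acceleration.
- **The median may be a sample-level figure, giving one common day.** The wording does not exclude this, and Fig. 2 is not shown. On a common day the problem would largely vanish. But the median is placed between the initial and final assessments, and the final one is each participant's closure. That favours the own-midpoint reading.
- **Early acceleration would show a benefit at the midpoint.** This also stands, so the midpoint is not blind to every effect. Nothing in the article says which phase LED should speed up, and a measure whose sign depends on the phase is not a measure of speed.
- **A rate in percent per day, on actual days, would avoid the defect.** It would, but the outcome section equates the rate with a percentage, and {20a} fits time as a factor.

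The point is not detail that an article leaves to an analysis plan, since the article states which three assessments are used and excludes the rest.

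**Conclusion.** On the natural reading of Participant timeline {13}, the mixed model for percent healed compares the shape of the closure curve between groups and not its speed. Even acceleration gives an expected difference of zero, whatever the curve. On a linear curve with a speed change at 50% healed, late doubling gives 37.5% against 50% and early doubling 62.5% against 50%. Of these three patterns only early acceleration shows as a benefit.

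The finding applies to the percent-healed component and to participants who reach closure, and it depends on the own-midpoint reading. Within those limits it is a stated rule that gives a wrong answer, and it should be corrected before outcomes are compared by group. The sample-size basis is affected too: the reproduced 30 averages a group effect over three measures, two of which have no between-group variation in percent healed.

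**What to change.** For percent healed, replace the own-midpoint and closure time points with an analysis on days since first treatment. Preferably model all the daily images already planned, with closed wounds entered as 100% from closure onward. Otherwise compare percent healed at common days named in advance, matched to the nearest visit because sessions take place five times a week. Keep days to healing as the direct measure of speed. If one common day was meant all along, say so and name it. The interim analysis {21b} is on the primary endpoint and should follow the same definition.

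Costs:

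- No new data are needed, but section {25} requires a formal amendment, notice to the ethics committee and an entry in the trial registry. Trial status says recruitment is under way.
- A single early day can miss late acceleration (8% of simulated trials significant at day 7).
- A later day has many wounds at the 100% ceiling (about 56% of sham and 92% of LED at day 14 under the stated assumptions), which fits poorly with normal residuals. Both are reasons to prefer the full daily series, and the ceiling needs attention there too.
- Sample size {14} should restate its basis for percent healed at the new time points.
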